#### App data

In the CR and CR + AFE conditions, the investigator will rate the credibility of participant’s display of emotions in their voice, facial expression, and body posture on a Likert scale from 0 to 5 via the EmpkinS-EKSpression app. The app will record timestamps for each action during the training. Moreover, it will record which statements participants selected to express approval/rejection, affirmation, and self-support in the CR and CR + AFE conditions.

### Statistical analysis plan

Analyses will be conducted via SPSS Version 29 for Windows [61] and R Studio [37]. While analyses will focus on a per-protocol approach, intention-to-treat-analyses using imputations for missing data will also be conducted. In accordance with the CONSORT statement [36], number and reasons for dropout will be recorded and reported for each condition.

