## Methods

### Design

To examine the relevance of kinesthesia for treatment and diagnosis of depression, we aim to conduct a four-armed, parallel, single-blind RCT (see Fig. 2) in accordance with the CONSORT statement [36]. The study is preregistered in the Open Science Framework (https://osf.io/mswfg/). It will be carried out at the EmpkinS Lab of the Friedrich-Alexander-Universität Erlangen-Nürnberg, structured around a smartphone-based training. There will be three intervention conditions: (1) a cognitive reappraisal training (CR), (2) CR enhanced by instructions to deliberately display anti-depressive facial expressions (CR + AFE), and (3) facial muscle training focusing on anti-depressive facial expressions (AFE). The control condition (4) will receive a sham intervention. Participants will be randomly allocated to one of the four study conditions with a 1:1 allocation ratio. A block randomization with a randomly varying block size of four or eight will be performed following a randomization list generated using the blockrand-package in R Studio [37]. To control for confounding expectation effects, participants will be blinded regarding the study condition they are allocated to, but will be debriefed after study completion. Moreover, to avoid biased assessments, researchers conducting the follow-up assessment will also be blinded to participants’ group allocation.

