### Participants

We will recruit two participant groups of equal size with differing diagnostic status: one group of individuals with clinically relevant depressive symptomatology and a control group of individuals without depression. The diagnostic groups will be matched according to gender and age. For the depression group, the main inclusion criterion is the presence of a diagnosis from the depressive spectrum according to ICD-10 criteria (F32 ‘depressive episode’, F33 ‘recurrent depressive disorder’, F34.1 ‘dysthymia’, and F43.20 & F43.21 ‘adjustment disorder with depressive symptoms’ [38]) according to the Structured Clinical Interview for DSM-5 Disorders - Clinician version (SCID-5-CV; German Version: [39]). The main inclusion criterion for the group without depression is a score < 10 on the Patient Health Questionnaire (PHQ)-8 [40]. Additional inclusion criteria for both groups include being ≥ 18 years, being able and willing to provide informed consent regarding study participation, and having sufficient German language skills (at least level B2 according to the Common European Framework of Reference for Languages). Exclusion criteria included the presence of any psychotic disorder (ICD-10 F2x), any substance dependence disorder other than nicotine (ICD-10 F1x.2), acute suicidality, any impairment of facial expression (e.g., due to facial paralysis or recent Botox treatment or autism spectrum disorder), and any type of dyschromatopsia. To ensure maximum external validity, we refrain from applying further potential exclusion criteria such as other clinical comorbidities, or concurrent pharmaco- or psychotherapy, but will record this information.

A power analysis was conducted with G*Power [41] to determine the necessary sample size for a 2-group-comparison of each of the intervention conditions (CR, CR + AFE, AFE) with the sham control condition. In absence of similar studies serving as reference for the determination of a critical effect, a team of three clinical experts agreed that an effect size of *d* = 0.5 would be therapeutically relevant. The power analysis yielded a necessary sample size of *n* = 32 for each of the four intervention conditions and two diagnostic groups based on a 2-sided analysis, a critical alpha-level of α = 0.05, and a power of β = 0.80. Hence, we will include *N* = 256 participants in total, composed in equal parts of participants with depression (*n* = 128) and without depression (*n* = 128).

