#### Feasibility measures

We will assess treatment integrity, compliance, usability, and acceptability to determine the feasibility of our intervention.

*Treatment integrity* is defined as study therapists’ adherence and competence (in accordance with [58]. A subsample (10%) of video-recorded training sessions will be used to rate treatment integrity. Adherence with the manual and therapist competence will be rated on a five-point Likert scale from 1 (*not at all*) to 5 (*very much*).

*Compliance* of participants in terms of commitment to the training will be rated by study therapists on a five-point Likert scale from 1 (*not at all*) to 5 (*very much*).

The *usability* of the intervention smartphone app will be operationalized with the short form of the User Experience Questionnaire (UEQ-S; [59]) and one self-generated item asking participants about the comprehensibility of the instructions in the app on a four-point Likert scale from 1 (*not at all*) to 4 (*very*). The UEQ-S consists of eight pairs of terms related to user experience with opposite meanings (e.g., complicated – easy) that are rated on a seven-point Likert scale from − 3 (*fully agree with negative term*) to + 3 (*fully agree with positive term*). The UEQ-S has two subscales (pragmatic quality and hedonic quality), and an overall indicator of user experience can be computed.

*Acceptability* of the training is operationalized with the ‘hedonic quality’ scale of the UEQ-S and 12 additional self-generated items, all rated on a four-point Likert scale from 1 (*not at all*) to 4 (*very*), and four open questions will be directed toward participants to gain feedback and suggestions for app improvement (see Supplementary Table 3 for the whole measure). Additionally, eight open-ended questions will be asked by the study therapist after the first and after the second training phases.

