#### Efficacy of the reappraisal training augmented with facial expressions

In order to study the effectiveness of the EmpkinS-EKSpression app-based interventions, generalized linear models (GLMs) of the between-subject factors “diagnostic group” (with depression vs. without depression) and “intervention condition” (CR vs. CR + AFE vs. AFE vs. sham control), as well as the within-subject factor “time of assessment” will be applied in a stepwise fashion.

Regarding the primary outcome of depressed mood, we will first examine whether the mood induction phase *induces* depressed mood using a paired *t*-test with the pre- and post-mood-ratings as dependent variable (manipulation check). Further, hierarchical linear models (HLMs) will be implemented to assess whether the EmpkinS-EKSpression app-based interventions are effective in *reducing* depressed mood. As a first step, we will compare the CR condition with the sham control condition and the CR + AFE with the CR condition to study whether cognitive reappraisal training can be augmented with anti-depressive kinesthesia. As a second step, we will compare the AFE condition with the sham control condition. For continuously assessed secondary outcomes (i.e., positive mood, app data), corresponding analyses will be conducted.

With regard to secondary outcomes (i.e., GRID-HAMD, CES-D, current suicidality, ERSQ-ES, DAS-A, ATQ-R) assessed at pre-treatment, post-treatment, and/or follow-up, as well as pre/post mood-ratings, we will implement mixed analyses of variance (ANOVAs), again with the between-subject-factor, “study condition” (CR, CR + AFE, AFE, sham control) and the within-subject factor, “time.” Feasibility measures (treatment integrity, compliance, usability, acceptability) will be descriptively analyzed and contrasted between study conditions utilizing one-way ANOVAs. Finally, changes in kinesthesia and other psychophysiological measures over the course of the intervention, as well as differences between diagnostic groups and intervention conditions will be examined using, again, HLMs. All analyses will be conducted using the whole sample, as well as with the added between-subject-factor, “diagnostic group” (with vs. without depression). All analyses will be conducted with a significance level of α = 0.05. One-tailed tests will be used when the algebraic sign of the test statistic is specified; otherwise, two-tailed tests will be used.

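### The per-protocol set leads the analysis of a randomised efficacy comparison; the analysis of all randomised participants should come first

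*Protocol article*

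**What the plan says.** The protocol article, under Statistical analysis plan, sets the order of the two analysis sets: "While analyses will focus on a per-protocol approach, intention-to-treat-analyses using imputations for missing data will also be conducted". The same paragraph promises dropout numbers and reasons by condition. No other section reverses the order or names a different primary set for depressed mood.

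The comparison is randomised (Design): "Participants will be randomly allocated to one of the four study conditions with a 1:1 allocation ratio". Its aim is efficacy. Under the heading on efficacy of the reappraisal training, hierarchical linear models are used "to assess whether the EmpkinS-EKSpression app-based interventions are effective in *reducing* depressed mood", with CR against sham, CR + AFE against CR, and AFE against sham. No non-inferiority or equivalence margin appears.

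The Participants section powers a "2-group-comparison of each of the intervention conditions (CR, CR + AFE, AFE) with the sham control condition", on the judgement that "an effect size of *d* = 0.5 would be therapeutically relevant". It arrives at 32 per condition and diagnostic group, 256 in all, with no stated allowance for losses.

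**The concern.** In a comparison meant to show that one condition lowers depressed mood more than another, randomisation protects the contrast only while everyone allocated is analysed as allocated. A per-protocol set is chosen after allocation. If the chance of leaving it depends on both the condition and the participant's mood, the remaining groups are no longer comparable, and the difference between them mixes treatment effect with selection.

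Here the conditions make different demands. CR and CR + AFE participants answer depressogenic and anti-depressive statements aloud, with acted expression in CR + AFE; AFE participants tense or relax facial muscles; sham participants sort geometric shapes. Allocation happens at the start of the training session, before the pre-assessment and a 90 to 120 minute intervention (Procedure), so there is room for exclusions after allocation. What is at stake is which estimate is reported as the trial's main result.

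**Working it through.** **1. The plan's own figure.** Inputs from Participants: d = 0.5, "based on a 2-sided analysis, a critical alpha-level of α = 0.05", power 0.80. For a two-sample t-test with n per group, the noncentrality is d × √(n/2). With n = 64 this is 0.5 × √32 = 2.83, and the noncentral t distribution gives power 0.801. The normal approximation gives n = 63. So 64 per condition (2 × 32, diagnostic groups pooled) and 4 × 64 = 256 reproduce. The planned total equals the required minimum.

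**2. Power if the analysed set is smaller.** Assume 6 of 64 are excluded (9.4%); the article gives no rate.
- 58 against 58: noncentrality 0.5 × √29 = 2.69, power 0.76.
- 58 against 64: power 0.78.

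**3. Bias under a true effect of zero.** Take one standard normal outcome per person, scored so that higher means better mood. In one condition, exclude the fraction q lowest on a score that correlates r with the outcome. The mean of those who remain shifts by

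r × φ(z_q) / (1 − q), where z_q is the q-quantile of the standard normal.

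With q = 6/64 = 0.094: z_q = −1.318, φ = 0.167, and 0.167/0.906 = 0.185.
- r = 0.3: shift 0.3 × 0.185 = 0.055.
- r = 0.5: shift 0.5 × 0.185 = 0.092.

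The standard error of the difference, allowing for the slightly reduced variance among those who remain, is 0.180 and 0.178. The standardised shifts are 0.31 and 0.52. The chance of exceeding +1.96 is 1 − Φ(1.96 − 0.31) = 4.9% and 1 − Φ(1.96 − 0.52) = 7.5%, against 2.5% with no bias. A simulation of 20,000 null trials gave d = 0.052 with 4.7%, and d = 0.089 with 7.1%, so the two methods agree to within half a percentage point.

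**4. Direction.** The calculation is symmetric. The same exclusions made in the comparator instead give d of about −0.05 to −0.09 and hide a benefit.

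**5. How far this depends on the pattern of exclusions.** Simulated with the same method:

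| Excluded (intervention / comparator) | r | Spurious d | Favourable two-sided rejection |
|---|---|---|---|
| 6 / 0 | 0.5 | 0.09 | 7.1% |
| 6 / 0 | 0.3 | 0.05 | 4.7% |
| 6 / 3 | 0.5 | 0.04 | 4.6% |
| 6 / 3 | 0.3 | 0.03 | 3.8% |
| 3 / 0 | 0.3 | 0.03 | 3.4% |
| 6 / 6 | 0.5 | 0.00 | 2.9% |

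Exclusion counts and correlations are assumptions throughout. The planned model uses repeated ratings; one outcome per person is a simplification.

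**The case against.** The strongest reply is that little may be at risk. Allocation, training and the mood ratings described under Primary outcome fall within one laboratory visit, during which a study therapist runs the app and supports the participant. Exclusions that touch the primary outcome may be few. Loss is more plausible at the two-week follow-up, which carries secondary outcomes. An intention-to-treat analysis is already planned and dropout will be reported by condition, so readers would see both results. The Discussion calls the study a proof of principle. All of this stands and limits the severity. It does not justify the order: if exclusions are few, putting all randomised participants first costs almost nothing, and if they are many or uneven, it is needed.

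Three stronger readings are tempting, and the article does not support them.
- A reader might infer that compliance decides who is excluded, since commitment "of participants in terms of commitment to the training will be rated by study therapists", who know the condition. The article treats this rating as a feasibility measure, to be described and compared between conditions. Nothing ties it to the per-protocol set. The absence of a definition is not itself held against the article, because a fuller plan commonly supplies it.
- A reader might infer that the bias favours the interventions. Sham participants also go through both mood inductions and may stop too, and CR + AFE against CR compares two demanding conditions. The direction is unknown.
- A reader might take the extreme case, in which exactly the six worst outcomes are dropped (d = 0.18, about 20% favourable rejection), as the size. No plausible per-protocol rule works that way.

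The power loss is modest, and analysing everyone as allocated recovers nothing from a participant who gave no ratings.

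**Conclusion.** The point holds as a matter of order. The article makes per-protocol the lead analysis of randomised efficacy contrasts, and that set can be biased by exclusions after allocation. The documents fix neither the size nor the sign of that bias. If 6 of 64 leave one condition only and exclusion correlates 0.3 to 0.5 with mood, the spurious effect is about a tenth to a fifth of the design effect (0.05/0.5 to 0.09/0.5), and favourable false positives rise from 2.5% to about 5% to 7%. If exclusions are balanced or few, the error is close to nominal. Separately, the favoured set is the one that the sample size makes no allowance for, although the shortfall is small. This should be fixed; the evidence does not show that the trial's result will be distorted.

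**What to change.** State that the primary analysis of depressed mood includes all randomised participants in the condition to which they were allocated. Either fit the planned hierarchical linear model to all available ratings, which is valid if ratings are missing at random, or use the imputation already planned. Make per-protocol a sensitivity analysis. Settle this before outcome data are analysed, because the order determines which estimate is the main result.

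The cost is one sentence. Both analyses are already planned, so there is no added work; the effect estimates may be slightly smaller.

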#### Preprocessing of kinesthesia and further psychophysiological data

Video data will be primarily processed with the FaceReader software [62], which offers an extensive array of visual features, including probabilities associated with basic emotions such as neutral, happy, sad, angry, surprised, scared, disgusted, and contempt - all discernible within each video frame. Additionally, it provides measurements of valence and arousal that are essential for understanding emotional states. Furthermore, it allows the extraction of so-called Facial Action Units (e.g., “Eyes Closed”, “Lip Stretcher”), offering insights into the intensity of expressions ranging between 0 and 1, and estimates head position and orientation in 3D (e.g., pitch, yaw, and roll rotation angles), complemented by 2D and 3D facial landmarks. The Facial Action Units and their variations provide detailed information on facial expressions and movements [63]. With regard to videos recorded with the Azure Kinect depth camera, we will extract depth information of body posture (i.e., the distance of each body part from the camera). Psychophysiological data, i.e., EMG, ECG, and respiration signals, will be preprocessed by extracting generic as well as specific features using various methods, particularly focusing on bio-signal feature extraction. Generic features of all psychophysiological data include mean, standard deviation, minimum, and maximum. Specific features of EMG signals include mean absolute value (MAV) and root mean square (RMS), specific features of ECG signals include heart rate and RR intervals, and specific features of respiration signals include respiration rate and respiration rate variability.

Cross-sectional comparisons between diagnostic groups (i.e., with vs. without depression) regarding baseline demographic, health-related, and clinical characteristics will be conducted using *t*-tests for continuous and Χ^2^-contingency tables for dichotomous variables, respectively.

#### Efficacy of the reappraisal training augmented with facial expressions

In order to study the effectiveness of the EmpkinS-EKSpression app-based interventions, generalized linear models (GLMs) of the between-subject factors “diagnostic group” (with depression vs. without depression) and “intervention condition” (CR vs. CR + AFE vs. AFE vs. sham control), as well as the within-subject factor “time of assessment” will be applied in a stepwise fashion.

Regarding the primary outcome of depressed mood, we will first examine whether the mood induction phase *induces* depressed mood using a paired *t*-test with the pre- and post-mood-ratings as dependent variable (manipulation check). Further, hierarchical linear models (HLMs) will be implemented to assess whether the EmpkinS-EKSpression app-based interventions are effective in *reducing* depressed mood. As a first step, we will compare the CR condition with the sham control condition and the CR + AFE with the CR condition to study whether cognitive reappraisal training can be augmented with anti-depressive kinesthesia. As a second step, we will compare the AFE condition with the sham control condition. For continuously assessed secondary outcomes (i.e., positive mood, app data), corresponding analyses will be conducted.

With regard to secondary outcomes (i.e., GRID-HAMD, CES-D, current suicidality, ERSQ-ES, DAS-A, ATQ-R) assessed at pre-treatment, post-treatment, and/or follow-up, as well as pre/post mood-ratings, we will implement mixed analyses of variance (ANOVAs), again with the between-subject-factor, “study condition” (CR, CR + AFE, AFE, sham control) and the within-subject factor, “time.” Feasibility measures (treatment integrity, compliance, usability, acceptability) will be descriptively analyzed and contrasted between study conditions utilizing one-way ANOVAs. Finally, changes in kinesthesia and other psychophysiological measures over the course of the intervention, as well as differences between diagnostic groups and intervention conditions will be examined using, again, HLMs. All analyses will be conducted using the whole sample, as well as with the added between-subject-factor, “diagnostic group” (with vs. without depression). All analyses will be conducted with a significance level of α = 0.05. One-tailed tests will be used when the algebraic sign of the test statistic is specified; otherwise, two-tailed tests will be used.

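### Five secondary symptom outcomes are tested in effect as change scores; adjusting the T4 value for its own baseline would sharpen the condition contrasts with no added participants

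*Protocol article*

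**What the plan says.** The section on efficacy of the reappraisal training assigns these secondary outcomes to one method: "GRID-HAMD, CES-D, current suicidality, ERSQ-ES, DAS-A, ATQ-R", described as "assessed at pre-treatment, post-treatment, and/or follow-up". For them, and for pre/post mood ratings, "we will implement mixed analyses of variance (ANOVAs), again with the between-subject-factor" study condition and the within-subject factor time. No baseline covariate is named.

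Table 1 fixes the occasions. GRID-HAMD, ERSQ-ES, DAS-A and ATQ-R are taken at T1 and T4, and CES-D at T2 and T4. Current suicidality is taken at T1, T2, T3 and T4.

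The same section says of diagnostic group: "All analyses will be conducted using the whole sample, as well as with the added between-subject-factor" for diagnosis. It does not say which of the two versions is the main one.

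The primary outcome, depressed mood, has a different main model: "hierarchical linear models (HLMs) will be implemented to assess whether the EmpkinS-EKSpression app-based interventions are effective" in lowering it.

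**The concern.** With one value before training and one after, the condition-by-time term asks whether mean change differs between conditions. A change score subtracts the whole baseline value, whatever its correlation with follow-up. Unless that correlation is very high, this adds baseline noise to the comparison. A model with baseline as a covariate estimates how much of it to subtract. Under randomisation both approaches estimate the same condition effect, so only precision differs.

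What is at stake is the width of the confidence intervals for the condition contrasts on five symptom and cognition scales. The Discussion itself expects a single session to have little effect on overall symptom severity, so avoidable noise matters for whatever small effects exist. Every baseline value needed is already scheduled.

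**Working it through.** **Inputs.** Occasions per outcome: Table 1. Effect size d = 0.5, two-sided alpha 0.05, power 0.80, and 32 per condition in each of two diagnostic groups: Participants section. That gives 2 × 32 = 64 per condition and N = 256. The correlation r is not given; I use 0.3 to 0.9.

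**The plan's own figure.** A two-group t-test with 64 per condition and d = 0.5 has power 0.801 (noncentral t). The stated size therefore reproduces for the whole sample. With 32 per condition, inside one diagnostic group, two-sided power is 0.50. None of what follows changes the sample size.

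**Baseline adjustment against change scores.** Take equal SDs of 1 at both occasions, and let r be the correlation within diagnostic group. The residual variance per person is:

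- change score: 1 + 1 − 2r = 2(1 − r)
- T4 adjusted for baseline: 1 − r²
- ratio: (1 − r)(1 + r) / [2(1 − r)] = (1 + r)/2

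| r | 2(1 − r) | 1 − r² | Ratio | Interval narrower by 1 − √ratio | Participants per condition for equal precision, 64 × ratio | Power after adjustment if the change test has 80% |
|---|---|---|---|---|---|---|
| 0.3 | 1.40 | 0.91 | 0.65 | 19% | 42 | 94% |
| 0.5 | 1.00 | 0.75 | 0.75 | 13% | 48 | 90% |
| 0.7 | 0.60 | 0.51 | 0.85 | 8% | 54 | 86% |
| 0.9 | 0.20 | 0.19 | 0.95 | 3% | 61 | 82% |

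The last column is the noncentral t power at 64 per condition for a standardised effect of 0.5/√ratio.

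Simulation (3,000 data sets per scenario, four conditions of 64, diagnostic groups 2 SD apart at baseline) gave variance ratios of 0.76 and 0.77 at r = 0.5 and 0.85 at r = 0.7. These agree with the formula.

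**Diagnostic group in a change analysis.** Let g be the difference in mean change between the diagnostic groups, in within-group SDs. With equal halves, leaving diagnosis out adds g²/4 to the residual variance of change.

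- g = 0: nothing is added, so including diagnosis gains nothing.
- g = 0.5: 1.00/1.0625 = 0.94 at r = 0.5 and 0.60/0.6625 = 0.91 at r = 0.7, a fall of 6% to 9%.
- g = 1.0: 1.00/1.25 = 0.80 and 0.60/0.85 = 0.71, a fall of 20% to 29%.

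With exactly 32 per cell the change-score estimate is identical with or without diagnosis; only its standard error can differ.

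**Why diagnosis belongs beside baseline.** Take r = 0.5, groups 2 SD apart and g = 0. Adjusting for baseline alone leaves a residual variance of 0.875, because the pooled correlation is 0.75. Adding diagnostic group brings it to the 0.75 in the table.

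**The case against.** A mixed ANOVA in a randomised trial is valid and unbiased, so nothing here is an error of inference. The outcomes are secondary, and the article calls effects on overall severity unlikely. T1 and T4 are about three weeks apart and T2 and T4 two weeks. If r is near 0.9, the variance falls by only 5% and the interval narrows by 3%. All of this stands and limits the weight of the point. It does not remove it, because the method is stated rather than left open and the better one needs no new data.

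Four stronger readings are tempting, and the documents do not support them.

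- *Diagnosis is left out of the analysis.* The whole-sample version omits it, but the same sentence plans every analysis again with it. What is missing is a statement of which version leads.
- *Omitting diagnosis widens every contrast and cuts power from 0.80 to 0.71–0.51.* Those figures follow for a comparison of levels with the diagnostic groups 1 to 2 SD apart. The efficacy section plans no such comparison: symptoms are tested by condition over time, where level differences cancel, and mood by HLM on repeated ratings.
- *Arms will be unbalanced on diagnosis.* The Design section says "A block randomization with a randomly varying block size of four or eight will be performed following a randomization list" and does not mention stratification. A condensed article's silence does not show there is none, and the Participants section sets 32 per condition in each diagnostic group. An imbalance in level would in any case cancel in the change comparison.
- *Participants without T4 are simply dropped.* The statistical analysis plan section puts the focus on a per-protocol approach but also plans intention-to-treat analyses with imputation.

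**Conclusion.** The point holds as a matter of efficiency for five secondary outcomes: GRID-HAMD, CES-D, ERSQ-ES, DAS-A and ATQ-R. Their planned condition-by-time test is a change-score test, and baseline adjustment would cut the variance of a condition contrast by 35% to 5% for r from 0.3 to 0.9. This rests on equal SDs at the two occasions and on a correlation that the documents do not give. With equal SDs the gain is positive for any r below 1.

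Naming diagnostic group in the main model adds precision to a change analysis only if the two diagnostic groups change differently. Current suicidality, with four occasions, is outside the change-score argument. The HLM for the primary outcome and the sample size of 256 are not called into question.

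**What to change.** For the five outcomes, replace the mixed ANOVA as main analysis by a linear model (ANCOVA, or an equivalent baseline-adjusted mixed model) of the T4 value on condition, the outcome's own baseline (T1; T2 for CES-D) and diagnostic group. State that this version, including diagnostic group, is the main one. Keep the condition-by-diagnostic-group interaction as a separate moderator test.

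The cost is a few lines of analysis wording. All covariates are already collected, and no visit, measure or participant is added. The article reports recruitment as ongoing, so the change should be dated and recorded before the outcome data are analysed.
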